## Abstract

**Background:**

Epilepsy is the most common neurological problem that affects people with learning disabilities. The high seizure frequency, resistance to treatments, associated skills deficit and co-morbidities make the management of epilepsy particularly challenging for people with learning disabilities. The Books Beyond Words booklet for epilepsy uses images to help people with learning disabilities manage their condition and improve quality of life. Our aim is to conduct a randomized controlled feasibility trial exploring key methodological, design and acceptability issues, in order to subsequently undertake a large-scale randomized controlled trial of the Books Beyond Words booklet for epilepsy.

**Methods/Design:**

We will use a two-arm, single-centre randomized controlled feasibility design, over a 20-month period, across five epilepsy clinics in Hertfordshire, United Kingdom. We will recruit 40 eligible adults with learning disabilities and a confirmed diagnosis of epilepsy and will randomize them to use either the Books Beyond Words booklet plus usual care (intervention group) or to receive routine information and services (control group). We will collect quantitative data about the number of eligible participants, number of recruited participants, demographic data, discontinuation rates, variability of the primary outcome measure (quality of life: Epilepsy and Learning Disabilities Quality of Life scale), seizure severity, seizure control, intervention’s patterns of use, use of other epilepsy-related information, resource use and the EQ-5D-5L health questionnaire. We will also gather qualitative data about the feasibility and acceptability of the study procedures and the Books Beyond Words booklet. Ethical approval for this study was granted on 28 April 2014, by the Wales Research Ethics Committee 5. Recruitment began on 1 July 2014.

**Discussion:**

The outcomes of this feasibility study will be used to inform the design and methodology of a definitive study, adequately powered to determine the impact of the Books Beyond Words intervention to improve the management of epilepsy in people with learning disabilities.

**Trial registration:**

http://ISRCTN80067039 (Date of ISRCTN assignation: 23 April 2014).

## Background

### Rationale

People with learning disabilities experience a disproportionate burden of ill health and are affected by twice the number of health issues prevailing in the general population: higher incidence of long-term conditions and health risks, poorer health outcomes and an increased risk of premature death [1–4]. Epilepsy is one of many long-term conditions affecting people with learning disabilities that burdens their lives and hinders their quality of life [5]. It is considered the most common neurological disorder in people with learning disabilities, with a reported prevalence of 16 to 44% [2, 5–8], compared to 0.4% to 1% in the general population [9, 10].

The clinical management of epilepsy in people with learning disabilities is complex, due to both the clinical characteristics of the condition, as well as physical and cognitive impairments affecting them. Seizures are frequent, atypical and often severe. Approximately 70% of all seizures are refractory to treatment [11–14]. Seizures are less well controlled than in the general population of people with epilepsy, and may be accompanied by co-morbid health, mental health, sensory-motor and communication issues [15–17]. Poorly controlled epilepsy can severely affect social relationships, work, daily activities, quality of life and mortality [18–20]. As a result, young people and adults with learning disabilities and epilepsy face higher risks of premature and avoidable death related to epilepsy than the general population [21]. In addition, research shows that poorly controlled seizures and seizure frequency are associated with increased costs [22]. Pennington *et al.* recently demonstrated increased costs in people with epilepsy and learning disabilities [23], with a total estimated cost per patient, per annum, of £64,000 (including accommodation and basic care).

Managing long-term conditions is challenging for all patients, irrespective of their abilities and co-morbidities. However, it is even more complex for those with learning disabilities, who may not have the knowledge, skills and support required to assess potential risks and cope with recurring seizures, prescribed medications and regular doctor appointments. Research suggests that access to specialist services is poor for people with epilepsy and learning disabilities [24]. For carers and families who are not trained in supporting self-management, caring for adults with ‘dual disabilities’ can be extremely challenging and increase the caregiver burden [5]. Despite its high incidence, little is known about the management of epilepsy in people with learning disabilities, and those who support them. Research suggests that people with learning disabilities and epilepsy lack skills training adapted to their needs and intellectual abilities, and often fail to adequately manage and control their epilepsy [20]. The standard of care offered to people with learning disabilities and epilepsy is significantly poorer than in the general population, as is the case for most disease areas affecting people with learning disabilities [24, 25].

Guidelines from the National Institute for Health and Care Excellence (NICE) state that patients with epilepsy and learning disabilities: ‘should be empowered to manage their condition as well as possible, and should receive appropriate information and education about all aspects of epilepsy […] accessible to people with additional needs such as physical, sensory or learning disabilities’ [26]; p.9.

The Books Beyond Words booklet *Getting on with Epilepsy* has been designed to help people with learning disabilities and epilepsy understand and manage their illness through images that have been tested with people with mild to severe learning disabilities. The intervention is based on the assumption that people with learning disabilities who cannot read and have limited communication abilities are visually literate. Although the success and impact of the Books Beyond Words booklets (over 30 available) have been recognized by several awards and collaborations with established patient organizations, they have not as yet been formally evaluated in controlled settings or routinely adopted in the United Kingdom National Health Service (NHS). The lack of conclusive data on the effectiveness of educational interventions for people with epilepsy and learning disabilities warrants further investigation [24, 26].

### Aim

We aim to conduct a randomized controlled feasibility trial exploring key methodological, design and acceptability issues, in order to subsequently undertake a large-scale randomized controlled trial of the Books Beyond Words booklet as an intervention for epilepsy in adults with learning disabilities.

### Objectives

Our objectives are to:Assess the feasibility of undertaking a randomized controlled trial of the Books Beyond Words intervention for epilepsy in people with learning disabilities.To explore the feasibility of collecting resource use and quality of life data so as to inform the design of the health economics component of a future definitive trial.Assess the study procedures’ and intervention’s acceptability among adults with learning disabilities, carers and health professionals.

## Methods/Design

### Study design and setting

We will use a two-arm, single-centre design and will conduct the study over a 20-month period at Hertfordshire Partnership University NHS Foundation Trust, United Kingdom. The trust runs five epilepsy clinics, managing 196 adults with learning disabilities and epilepsy. The patients are seen on average once a month. We will randomly allocate eligible participants to an intervention arm (provision of the Books Beyond Words booklet *Getting on with Epilepsy*) and control arm (routine information and services), and will recruit participants over six months.

### Participants

Eligible participants will be identified by the consultant psychiatrists who run the epilepsy clinics. Each psychiatrist will compile a log of potentially eligible patients from existing records and from new referrals using the following criteria.

#### Inclusion criteria

The inclusion criteria for this study are as follows:Male and female patients, over 18 years of age.A confirmed clinical diagnosis of epilepsy (according to medical notes) and at least one seizure over the past 12 months.A confirmed clinical diagnosis of a learning disability (significantly below-average general intellectual functioning, and an IQ below or equal to 70).Meaningful communication that enables the patient to tell or follow the Books Beyond Words story, as judged by the carer and/or health professional.The carer is sufficiently proficient in English to read and complete the questionnaires with the patient.

#### Exclusion criteria

The exclusion criteria for this study are as follows:Vision impairment.Confirmed diagnosis of dementia.Have used the Books Beyond Words booklet for epilepsy in the past 12 months.

## Consent

Each consultant psychiatrist at the participating epilepsy clinics will send an invitation letter and two information sheets to the carers of all eligible patients with learning disabilities and epilepsy registered at the clinics. In accordance with the Mental Capacity Act 2005 [27], an easy-read information sheet and invitation letter will be intended for the patient and another information sheet for the carer. In the information sheet, carers will be asked to encourage patients who have the capacity to read and understand (or to be read to and understand) the easy-read information sheet to do so. For patients who lack the mental capacity to understand the information sheet, consent will be obtained from the patient’s carer. It will be the carer’s role to use what they know of the patient’s wishes and feelings about research to decide whether they would like to take part in the study.

After a week, the research nurse will invite carers and patients by phone, to attend a meeting at the epilepsy clinic. During this appointment, the research nurse will review the patient information sheets with both the patient and the carer, and will take consent from the patient, with the carer’s involvement and advice, using an easy-read consent form. For patients who lack the capacity to consent, the research nurse will use a consultee declaration form, which will be completed and signed by the carer. The research nurse will also inform the patient’s GP of their participation in the feasibility trial.

### Randomization

During the initial appointment with the research nurse at the epilepsy clinic, and after consent has been taken, the carer will complete the baseline questionnaire. Randomization will be managed by the Norwich Clinical Trials Unit (NCTU). Once consent is obtained and the baseline data registered, the research nurse will allocate the patient to the intervention or control arm, as instructed by the randomization website. All authorized users, including the research nurse, will login using their unique username and password to a secure website to randomize each participant. The results will be stored in a study database on the Norwich Clinical Trials Unit (NCTU) secure server at the University of East Anglia (no user identifiable data will be stored in the randomization database). Web traffic will be encrypted using standard secure sockets layer technology. The randomization (1:1 allocation ratio) will be ‘blocked’ into groups of six codes to reduce the imbalance of control and intervention group participants at any time.

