**The Books Beyond Words intervention.**

#### How the Books Beyond Words intervention will be used

After giving consent and completing the baseline questionnaires, patients in the intervention condition will use the booklet with the research nurse and carer, in a quiet room at the epilepsy clinic. The nurse will go through the booklet with each patient at their own pace. Health professionals and carers can create their own story with the patient or use the story provided at the end of the booklet. The booklet contains instructions for use and a list of useful resources and services. The research nurse will show the first picture of the booklet to the person with learning disabilities, who should be encouraged to hold the book and turn the pages at their own pace. Depending on the patient’s communication abilities and reactions, it is advised that the research nurse will prompt them to say what is happening, whether this has happened to them before, and how they feel about it. We anticipate that it may take up to one hour to go through the booklet. If the intervention cannot be explored in one sitting, the research nurse will arrange a further appointment. The patient will also be given a copy to take home and explore with the carer and/or relatives.

It is recommended that the patient is given the opportunity to use the book at least twice more at home over the study duration. The research nurse will call each carer two weeks after randomization to remind them that the patient should be given opportunities to use the booklet at least twice more. Use of the book at home with the carer or other relatives will be monitored as part of the follow-up assessments. The carers will not receive any formal training in using the booklet, but will be able to watch an online video and training slides explaining how to use the book with the person they care for. A link to the training video and slides will be provided by the nurse at the end of the initial meeting. The research nurse will receive a half-day training course in using the intervention.

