### Sample size and feasibility of recruitment

The present study aims to assess the variation in the primary outcome measure between groups from baseline to the 12-week follow-up assessment, in order to determine whether the intervention is likely to achieve a 10% increase in the participants’ quality of life [32]. This would equate to an effect size of approximately 0.4, requiring a total sample size of 174 in a full study (1-β = 0.8, α = 0.05). Based on the requirement of 9% of the total sample size in each group, this indicates a required sample size of 16 per group, and will enable the exclusion of an effect size of <0. Given a potential 25% dropout rate, a sample size of 20 per group (40 participants in total) will be targeted. However, the study team, the selected study design and recruitment procedures will aim to minimize all potential dropouts whenever possible.

Recent audit data indicates that there were 196 patients with epilepsy and learning disabilities registered at the Hertfordshire Partnership University NHS Foundation Trust in May 2013. A preliminary screening exercise has already been undertaken by the lead consultant psychiatrist, at each epilepsy clinic, confirming that 112 out of 196 patients meet the study’s inclusion criteria. This does not include new referrals, who will be screened for eligibility once recruitment commences. The study will therefore aim to recruit approximately 36% of eligible patients.

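### A single fixed block size of six lets the research nurse who books, consents and allocates patients foresee some allocations: up to about 9 of 40 with certainty

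*Protocol article*

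**What the plan says.** The Randomization section of the protocol article allocates 1:1, blocked "into groups of six codes to reduce the imbalance of control and intervention group participants at any time". It gives one size, six, and mentions neither variation in size nor strata. The target, under Sample size and feasibility of recruitment, is "a sample size of 20 per group (40 participants in total) will be targeted".

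The research nurse appears at each step of entry:
- Booking (Consent): "the research nurse will invite carers and patients by phone, to attend a meeting at the epilepsy clinic".
- Consent (same section): "the research nurse will review the patient information sheets with both the patient and the carer, and will take consent from the patient".
- Allocation (Randomization): "the research nurse will allocate the patient to the intervention or control arm, as instructed by the randomization website". This follows consent and registration of the baseline data. The same section lets other people with login rights randomize as well.
- Delivery (How the Books Beyond Words intervention will be used): "The nurse will go through the booklet with each patient at their own pace". This applies to the intervention arm. The Control group section gives controls routine information and services only.

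The Data analysis and Sample size sections compare ELDQOL between groups and use a one-sided 80% interval to judge whether a 10% gain is plausible.

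**The concern.** The web system hides the stored code, but it does not stop someone inferring the code from earlier results. A nurse who has seen the allocations so far, and knows that each six contain three of each arm, knows the next one as soon as one arm is used up within the block. Short of that, the arm that is behind is the better guess.

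If the person who arranges entry can foresee allocations, more engaged carers could be booked into, or encouraged towards, one arm. Carers complete the questionnaires, so such a difference could carry into ELDQOL. The size of any resulting bias cannot be worked out from the document. What can be worked out is how predictable the list is.

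**Working it through.** The article states no predictability figure, so there is none to reproduce.

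**Inputs.** Block size 6 and ratio 1:1, hence three codes per arm per block (Randomization). N = 40 (Sample size). Assumptions: one recruiter who sees every allocation, and one unstratified list. Certain knowledge also requires that the block size is known.

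**One block.** There are C(6,3) = 20 equally likely sequences. An allocation is certain when earlier ones have used up an arm. The best guess is otherwise the arm with more codes left.

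| Place in block | Chance it is certain | Chance the best guess is right |
|---|---|---|
| 1 | 0 | 0.5 |
| 2 | 0 | 3/5 = 0.6 |
| 3 | 0 | 0.6 × 0.5 + 0.4 × 3/4 = 0.6 |
| 4 | 2/20 = 0.1 | 0.1 × 1 + 0.9 × 2/3 = 0.7 |
| 5 | 8/20 = 0.4 | 0.4 × 1 + 0.6 × 0.5 = 0.7 |
| 6 | 1 | 1 |
| Sum | 1.5 (25% of 6) | 4.1 (68% of 6) |

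**Forty patients.** 40 = 6 × 6 + 4, that is, six full blocks and four places of a seventh.
- Certain: 6 × 1.5 + 0.1 = 9.1, and 9.1/40 = 23%.
- Guessed correctly: 6 × 4.1 + (0.5 + 0.6 + 0.6 + 0.7) = 24.6 + 2.4 = 27.0, and 27.0/40 = 67.5%, against 20 by chance.

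**If each of the five clinics had its own list** (assume 8 patients each, so one full block plus two places):
- Certain: 5 × 1.5 = 7.5.
- Guessed correctly: 5 × (4.1 + 0.5 + 0.6) = 26.

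**If patients are booked ahead.** The figures above apply just before randomization. Steering through booking order needs the knowledge earlier.
- One patient already booked ahead, who then enters: place 5 is known with chance 0.1 and place 6 with chance 0.4, so 0.5 per block, or 6 × 0.5 = 3.0 of 40.
- Two booked ahead: 0.1 per block, or 6 × 0.1 = 0.6 of 40.

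**Randomly varying sizes** (simulation, 3,000 lists of 40; the guesser knows the set of sizes but not their order):

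| Sizes | Certain, of 40 | Guessed correctly, of 40 |
|---|---|---|
| 6 only | 9.1 | 27.0 (67%) |
| 4, 6 | 2.3 | 27.6 (69%) |
| 4, 6, 8 | 0.9 | 27.1 (68%) |

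The last column barely moves, for a simple reason. Every completed block is level, so the arm behind in the running totals is also the arm behind in the current block, whatever its size. The best guess therefore needs only the running totals.

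**The case against.** Central web allocation after consent and baseline is a real safeguard, and the article gives a reason for blocking. Several stronger readings go beyond the text:

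- **That the nurse treats every patient.** The booklet session is for the intervention arm only. The nurse knows both arms through performing the allocation.
- **That one nurse randomizes everyone from one running list.** The singular wording suggests one nurse, but other users may randomize, and the article is silent on strata. Several users who did not share results would lower predictability.
- **That the block size was published during recruitment.** Trial status shows that the article was written with recruitment open, ending around March 2015. The document gives no publication date.
- **That judging capacity is a route to steering.** Under Consent and Ethical considerations, patients who lack capacity can enter through a consultee declaration by the carer. Capacity decides which form is used, not who is enrolled.
- **That the nurse chooses who is eligible.** Psychiatrists compile the log against the criteria and write to the carers of all eligible patients.

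All of this stands and narrows the point. What remains is the order of calling and booking, and encouragement to join. That room is not nil, because only 40 of 112 eligible patients (36%) are needed.

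It is also fair that the trial is mainly about feasibility and that its Discussion disclaims any demonstration of effect. Counts of recruitment, completion and withdrawal are little affected.

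**Conclusion.** The point holds as a modest design weakness that is cheap to improve. Fixed blocks of six make 9.1 of 40 allocations certain and 67.5% guessable, given a single recruiter, a single list and, for the certain ones, a known block size. These are upper bounds: separate clinic lists lower them to 7.5 certain and 26 guessed, one patient booked ahead lowers the certain ones to about 3, and independent users would lower them further. What is exposed is the between-group ELDQOL estimate and its one-sided 80% interval. A reader might infer that this estimate is biased or that the feasibility results are undermined. The document supports neither: it shows an opportunity, not its use, and no bias in ELDQOL can be quantified from it.

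**What to change.** Have the Norwich Clinical Trials Unit generate the remaining list in permuted blocks of randomly varying size, for example 4, 6 and 8. The sizes should be held at the unit and withheld from the nurse, the clinics and any publication until recruitment closes. Amend the Randomization section to say that block sizes vary at random and are not disclosed, without listing them.

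This takes certain allocations from 9.1 to about 1 of 40 even if the set of sizes leaks, and concealing the sizes protects against that remainder. It does not remove the guessing advantage, which stays near 68%, so the report should acknowledge the residual predictability.

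The cost is a regenerated list and one revised sentence. The downside is a possibly slightly larger imbalance: within a block the greatest difference between arms rises from 3 (half of six) to 4 (half of eight). An exact 20:20 split is not guaranteed now either, because 40 is not a multiple of six. If recruitment has closed, report the fixed block size as a limitation of the ELDQOL comparison and use varying, undisclosed blocks in the definitive trial.

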### Intervention group

The Books Beyond Words booklet *Getting on with Epilepsy* uses pictures to tell the story of a young man with learning disabilities and epilepsy who progressively learns how to better manage his condition and recurrent seizures (see Figure 1). The intervention aims to improve seizure control, reduce the risk of falls and seizure-related injuries and improve quality of life. It also aims to illustrate best practice and promote access to relevant services. The Books Beyond Words booklet for epilepsy was developed over an 18-month period, by an editorial team of consultants in psychiatry and neurodevelopmental psychiatry, a speech and language therapist and an illustrator. They were supported by an advisory group of medical experts in the field of epilepsy and learning disabilities, by adults with learning disabilities and their carers, voluntary organizations and advocacy groups. Several iterations were developed and tested with a wide group of stakeholders, including adults with mild to severe learning disabilities and epilepsy [28].

